**Results**		
**Numbers randomized**	Number of participants randomized to each group	For all three strategies, 12 general practices (clusters) will be recruited, involving 10 patients per practice to be invited for using PatientCoach per general practice.
**Recruitment**	Trial status	Recruitment of patients is ongoing
**Numbers analysed**	Number of participants analysed in each group	Not applicable.
**Outcome**	For the primary outcome, a result for each group and the estimated effect size and its precision	Not applicable.
**Harms**	Important adverse events or side effects	Not applicable.
**Conclusions**	General interpretation of the results	This study provides insight in the amount of support that is required by general practices for cost-effective implementation of IBSM. Additionally, design and results can be beneficial for implementation of other self-management initiatives in clinical practice.
**Trial registration**	Registration number and name of trial register	the Netherlands National Trial Register NTR2970
**Funding**	Source of funding	This study is supported by grants from: - The Netherlands Organisation for Health Research and Development (ZON-MW 80-82315-97-10004) - The Netherlands Asthma Foundation (NAF 3.4.09.011) - Funding for this publication was obtained from the Netherlands Organisation for Scientific Research (NWO) Incentive fund Open Access publications - - Hand-held electronic lung function meters for patients (PikO-1, Ferraris Respiratory, Hertford, United Kingdom) were provided by GlaxoSmithKline (GSK), Zeist, the Netherlands

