**Methods/design:**

This study is a three-arm cluster randomized trial with a cluster pre-randomisation design and 12 months follow-up per practice comparing the following three IBSM implementation strategies: minimum strategy (MS): dissemination of the IBSM program; intermediate strategy (IS): MS + start-up support for professionals (*i.e.*, support in selection of the appropriate population and training of professionals); and extended strategy (ES): IS + additional training and ongoing support for professionals. Because the implementation strategies (interventions) are primarily targeted at general practices, randomisation will occur at practice level.

In this study, we aim to evaluate 14 primary care practices per strategy in the Leiden-The Hague region, involving 140 patients per arm. Patients aged 18 to 50 years, with a physician diagnosis of asthma, prescription of inhaled corticosteroids, and/or montelukast for ≥3 months in the previous year are eligible to participate. Primary outcome measures are the proportion of referred patients that participate in IBSM, and the proportion of patients that have clinically relevant improvement in the asthma-related quality of life. The secondary effect measures are clinical outcomes (asthma control, lung function, usage of airway treatment, and presence of exacerbations); self-management related outcomes (health education impact*,* medication adherence, and illness perceptions); and patient utilities. Process measures are the proportion of practices that participate in IBSM and adherence of professionals to implementation strategies. Cost-effective measurements are medical costs and healthcare consumption. Follow-up is six months per patient.

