#### Blinding and strategy allocation

General practices (*i.e.*, 2,300 patients per ‘standard practice’) will be the unit of randomisation. Practices will be stratified according the following characteristics: postal code (area) and practice size (practices with <4 GPs are defined as a small practice, practices with ≥4 GPs as a large practice). Prior to informed consent, practices will be randomized into one of the strategies (1:1:1 ratio), in order to assess the participation level of practices per strategy. Practices will receive a letter containing information on the allocated implementation strategy and an invitation to participate in the project.

Both practices and patients will be blinded to group allocation. Researchers will not be blinded for group allocation. Randomisation will be conducted by [name] using a computer-generated, permuted-block scheme. General practices will be invited until enough practices per strategy are participating. General practices will be enrolled by [name], [name], and [name]. Patients will be enrolled by general practices.

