#### Sample size calculation

The sample size is based on patient participation in IBSM (primary outcome). We assume that one-third of the 15% to 20% of patients who have a written action plan
[9] are actually using it to conduct self-management activities. Assuming that with the MS, 5% of the patients are frequently using the IBSM to monitor their asthma, we will consider the IS and ES successful if an increase of 25% is achieved (alpha 0.05 and beta 0.20). Using a correction for clustering of patients in practice (intra-cluster correlation coefficient: 0.25), we calculated that we need 10 patients in each of 42 practices 14 practices in the MS, IS, and ES, respectively to be invited to participate in IBSM using PatientCoach. This gives a total of 420 patients.

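### The CONSORT table sets 12 practices per strategy, but the abstract and the sample size section set 14; the target must be reconciled and the sample size formula stated

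*Protocol article*

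**What the plan says.** The protocol article gives the number of practices per strategy in three places.

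- Abstract, *Methods/design*: "we aim to evaluate 14 primary care practices per strategy in the Leiden-The Hague region, involving 140 patients per arm".
- *Sample size calculation*: "we need 10 patients in each of 42 practices 14 practices in the MS, IS, and ES, respectively", followed by "This gives a total of 420 patients".
- Table 1 (CONSORT checklist), row *Numbers randomized*: "For all three strategies, 12 general practices (clusters) will be recruited, involving 10 patients per practice".

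The planning assumptions are in *Sample size calculation*: "Assuming that with the MS, 5% of the patients are frequently using the IBSM to monitor their asthma", then "we will consider the IS and ES successful if an increase of 25% is achieved (alpha 0.05 and beta 0.20", with an intra-cluster correlation of 0.25. The section does not name the test, its sidedness, any continuity correction or any adjustment for two comparisons.

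*Blinding and strategy allocation* describes when recruitment ends: "General practices will be invited until enough practices per strategy are participating". It gives no number.

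**The concern.** Two prospective targets are stated for the same quantity. They differ by 2 practices per strategy, 6 practices overall (42 − 36) and 60 patients (420 − 360, or 14% of 420).

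Loss of practices during the trial does not explain the gap, because it would run the wrong way: 12 is the number to be recruited, and 14 the number to be evaluated.

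The recruitment rule refers to a sufficient number of practices without saying what it is, so whoever applies it must take the number from elsewhere in the article and will find two. If 12 were used, the trial could fall short of the stated 80% power for patient participation, the outcome on which it is sized.

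**Working it through.** **Inputs** (*Sample size calculation*): p1 = 0.05 under the minimum strategy; p2 = 0.30, reading the 25% as percentage points; alpha 0.05; power 0.80; intra-cluster correlation 0.25; 10 patients per practice. Two-sided testing is an assumption, because sidedness is not stated.

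**Design effect:** 1 + (10 − 1) × 0.25 = 3.25.

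**Uncorrected n per arm**, with d = 0.25 and mean proportion 0.175:

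n = [z(alpha/2) × √(2 × 0.175 × 0.825) + z(power) × √(0.05 × 0.95 + 0.30 × 0.70)]² / d²

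= [1.960 × 0.5374 + 0.8416 × 0.5074]² / 0.0625 = 35.06, rounded up to 36.

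**With continuity correction:** n′ = (n/4) × [1 + √(1 + 4/(n × d))]² = 42.7, rounded up to 43.

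**Reproducing the stated 14:**

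| Method | n per arm | × 3.25 | Practices per arm |
|---|---|---|---|
| Two-sided 0.05, continuity correction | 43 | 139.75 | 14 |
| Two-sided 0.025 (two comparisons), no correction | 43 | 139.75 | 14 |
| Two-sided 0.05, no correction | 36 | 117 | 12 |
| One-sided 0.05, continuity correction | 36 | 117 | 12 |
| One-sided 0.05, no correction | 28 | 91 | 10 |

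Unpooled-variance and arcsine versions (two-sided 0.05) give 11 practices. So two of the methods tried return the stated 14 practices and 140 patients, and the plain two-sided formula returns the 12 in Table 1.

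**Power at each target.** The effective n per arm is 120/3.25 = 36.9 for 12 practices and 140/3.25 = 43.1 for 14.

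Uncorrected power = Φ{[d × √n − z(alpha/2) × 0.5374] / 0.5074}. The corrected version replaces d by d − 1/n.

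- At 12 practices, corrected: (0.2229 × 6.076 − 1.0532)/0.5074 = 0.594, power 72.4%.
- At 12 practices, uncorrected: (0.25 × 6.076 − 1.0532)/0.5074 = 0.918, power 82.1%.

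| Method | 12 practices | 14 practices |
|---|---|---|
| Two-sided 0.05, continuity correction | 72.4% | 80.4% |
| Two-sided 0.025, no correction | 73.2% | 80.5% |
| Two-sided 0.05, no correction | 82.1% | 87.7% |

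**Meaning of the 25%.** Read as a relative increase (5% to 6.25%), the corrected two-sided formula needs 5,491 × 3.25 ≈ 17,850 patients per arm. Only the percentage-point reading is compatible with 420 patients.

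**The case against.** A reader might infer that the trial has 72% power by its own method, or that only 14 follows from the stated inputs. Neither is supported. The protocol names no method; the continuity correction is inferred because it lands on 14, and the alpha 0.025 version lands there too. The plain two-sided formula applied to the same inputs gives exactly 12 practices, with power above 80%. The 12 may come from such a calculation.

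A reader might also infer that recruitment will stop at 12. The text does not say so. The recruitment rule does not point to Table 1, which is a reporting checklist, while the section that derives the number and the abstract agree on 14. Ten patients per practice is also a minimum (*Recruitment of general practices and patients*, *Patients*), so the 60-patient difference compares minimum targets.

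These objections stand and limit the claim about power. They do not remove the contradiction. If the uncorrected formula was used, 12 practices are enough and the statement that 14 are needed is wrong; if either method giving 14 was used, Table 1 is wrong. The two figures cannot both be the target.

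The 25% wording is a matter of clarity only, since the stated sample size already settles its meaning.

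**Conclusion.** The point holds as an internal contradiction in the sample size: 12 versus 14 practices per strategy, with no explanation in the article. A loss of power is possible but not established. Power at 12 practices is 72–73% under the two methods found that yield 14, and 82% under the plain uncorrected formula. These figures assume 5% versus 30%, two-sided testing, an intra-cluster correlation of 0.25, exactly 10 patients per practice and equal cluster sizes. Because the recruitment rule gives no number of its own and Table 1 reports patient recruitment as ongoing, the figure should be corrected rather than left to interpretation.

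**What to change.** - Change the *Numbers randomized* row of Table 1 to 14 practices and 140 patients per strategy, in line with the abstract and the sample size section.
- If 12 is the real target, correct the abstract and the sample size section instead (36 practices, 360 patients). Restate the power for 12 practices with the formula used: 72–73% under the methods that give 14, or 82% uncorrected.
- In either case, name the formula in *Sample size calculation*: sidedness, continuity correction and any adjustment of alpha. Give the target number where the recruitment rule is described.
- Minor: write the effect as an increase from 5% to 30% (25 percentage points).

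The cost is one table cell and a sentence or two of text if 14 stands. If 12 stands, the abstract and the sample size section also need new totals and a restated power. The design does not change.

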### Recruitment of general practices and patients

#### Eligibility criteria general practices

All general practices located within the Leiden – the Hague region and a GP/PN that is willing and available to support patients in IBSM will be eligible. Additionally, at least one GP per practice needs to give consent for participation.

#### Patients

General practices will be asked to invite at least ten 10 patients per practice to participate in IBSM. Based on previous studies on asthma within general practice, we know this is feasible
[16]. Those patients not willing to participate in IBSM will be asked informed consent to participate in an endpoint evaluation at six months. Informed consent will be obtained during a consultation with a patient’s PN or GP.

#### Endpoint evaluation

Patients in practices randomized to the MS strategy, and those patients in the IS and ES strategy not willing to participate in IBSM support, will only be approached for an endpoint evaluation at six months after their start with PatientCoach.

#### Eligibility criteria patients

Patients, age 18 to 50 years, with a doctor diagnosis of asthma and prescription of inhaled corticosteroids and/or montelukast for at least three months in the previous year who have access to the internet are eligible to participate.

#### Exclusion criteria patients

Those who have severe co-morbidities (*i.e.*, terminal illness or a severe psychiatric disease), daily or alternate day oral corticosteroid therapy for at least a month before entering the study, or who are primarily under treatment by a respiratory physician are not eligible. Furthermore, the IBSM support program is not suitable for those who are unable to understand written and oral Dutch instructions.

#### Blinding and strategy allocation

General practices (*i.e.*, 2,300 patients per ‘standard practice’) will be the unit of randomisation. Practices will be stratified according the following characteristics: postal code (area) and practice size (practices with <4 GPs are defined as a small practice, practices with ≥4 GPs as a large practice). Prior to informed consent, practices will be randomized into one of the strategies (1:1:1 ratio), in order to assess the participation level of practices per strategy. Practices will receive a letter containing information on the allocated implementation strategy and an invitation to participate in the project.

Both practices and patients will be blinded to group allocation. Researchers will not be blinded for group allocation. Randomisation will be conducted by [name] using a computer-generated, permuted-block scheme. General practices will be invited until enough practices per strategy are participating. General practices will be enrolled by [name], [name], and [name]. Patients will be enrolled by general practices.

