## Methods

### Study design

This study is a three-arm, cluster randomized trial with a cluster pre-randomisation design
[7] (Figure 
1). Because the implementation strategies are primarily targeted at general practices, randomisation will occur at practice level (CONSORT guidelines for cluster trials, Table 
1[27]). Prior to obtaining informed consent from GPs and patients, practices will be allocated to one of the strategies. Follow-up per practice is 12 months. At patient level, follow-up duration is six months. In the ES and IS strategies, individual patient outcomes will be evaluated at baseline (first visit of a patient to the general practice for instruction on IBSM), and three and six months after a patient’s start with IBSM. Individual patient outcomes in the MS strategy will be evaluated at six months (end-point evaluation) after a patient’s start with IBSM.

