		Instruction visit on how to use PatientCoach, particularly focusing the essential self-management skills in asthma (i.e., monitoring, inhalation technique). Patients will be instructed to monitor their level of asthma control at least once per month, preferably once weekly using the Asthma Control Questionnaire. General practices themselves can decide whether the practice nurse and/or general practitioner guide patients in using PatientCoach. Follow-up per patient is six months. However, patients will have the possibility to continue using PatientCoach.nl after this period.
**Objective**	Specific objective or hypothesis	The objectives of this study are to investigate the effectiveness and cost- effectiveness of a Minimum strategy, as compared to an Intermediate strategy and an Extended strategy in a three arm cluster-randomized trial. Since these different implementation strategies have a sequence of effects, the evaluation is aimed to assess to what extent: 1. practices participate in IBSM (practice level); 2. IBSM improves asthma related quality of life (patient level); 3. patients participate in IBSM (patient level); and 4. The various implementation strategies are cost-effective (societal/organisational level)
**Outcome**	Clearly defined primary outcome for this report	Primary outcome measures are a) the proportion of referred patients that participate in IBSM (general practice (cluster) and patient level) and b) the proportion of patients that have clinically relevant improvement in the asthma-related quality of life as measured by the Asthma Quality of Life Questionnaire [30].Patient usage of IBSM is defined as two out of three months ACQ-monitoring compliance.
**Randomisation**	How participants were allocated to interventions	As the implementation strategies (interventions) are primarily targeted at general practices, randomisation will occur at practice level.
		General practices (i.e., 2,300 patients per ‘standard practice’) are the unit of randomisation. Prior to informed consent all general practices in the Leiden-the Hague region will be allocated to one of the three strategies (1:1:1 ratio). General practices receive a letter with information on the allocated strategy and an invitation to participate in the project.

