		Randomization will be conducted by [name] using a computer-generated, permuted-block scheme. Practices will be stratified according the following characteristics: postal code (area) and practice size (practices with < 4 general practitioners are defined as a small practice, practices with ≥4 general practitioners as a large practice.
		General practices will be enrolled by [name], [name] and [name]. Patients will be enrolled by general practices.
**Blinding (masking)**	**Whether or not participants, care givers, and those assessing the outcomes were blinded to group assignment**	All general practices and patients are blinded to group allocation. Researchers are not blinded for group allocation.

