#### Start-up support package

The start-up support intermediate package consists of: Practice recruitment. General practices receive an invitation letter that includes all components of the Start-up Support Implementation strategy. Non-responding practices receive a reminder letter within four weeks and if necessary, practices are phoned.

On-site support for patient recruitment. PatientCoach team members offer practices the opportunity to make a patient selection in the patient registries of participating GPs.

PatientCoach start-up training. PNs and GPs are invited for an interactive session (duration: two hours) with colleagues. In this session, professionals are stimulated to discuss with each other on how to apply IBSM in their own practice. This training is focused on a proactive attitude toward patients and supporting them in their self-management skills by using IBSM support:

1. Exploration of a patient’s knowledge about asthma, illness perceptions
[36,37], and the ability to integrate (internet-based) self-management activities into their daily life; *i.e.*, by exploring difficulties and discussing solutions.

2. Asthma control: assessment of the level of asthma control; patients are invited to discuss their most recent ACQ-score. Reasons for poor asthma control in patients are discussed, and the subsequent management strategy will be discussed.

3. Medication: information on side-effects; instruction, exploration of therapy adherence, and checking correct inhaler technique.

4. Asthma related lifestyle: smoking cessation, avoidance of triggers, regular exercise;

5. Asking about and treating rhinitis, which is known to influences asthma outcomes
[38].

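### Practices are said to be blinded to allocation, yet each is told its own strategy before it consents and before it chooses the patients who form the denominator of the first primary outcome

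*Protocol article*

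**What the plan says.** Two statements on blinding appear in the protocol article. The section Blinding and strategy allocation says "Both practices and patients will be blinded to group allocation". The blinding row of Table 1 (CONSORT checklist) says "All general practices and patients are blinded to group allocation". Both places add that researchers are not blinded.

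The same two places describe disclosure of the allocation. Blinding and strategy allocation says "Practices will receive a letter containing information on the allocated implementation strategy and an invitation to participate in the project". The randomisation row of Table 1 says "General practices receive a letter with information on the allocated strategy and an invitation to participate in the project". For the intermediate strategy (IS), Start-up support package is more specific: "General practices receive an invitation letter that includes all components of the Start-up Support Implementation strategy".

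On timing, Study design says "Prior to obtaining informed consent from GPs and patients, practices will be allocated to one of the strategies". On recruitment, Blinding and strategy allocation says "Patients will be enrolled by general practices". The section Patients adds that each practice is asked to invite at least ten patients and that consent is taken in a consultation with the practice nurse or GP.

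**The concern.** A practice that has been sent a description of its allocated strategy, and then takes part in that strategy, is not blinded to its allocation. The sentence claims a property that the design does not have for the people who recruit.

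In a cluster trial the blinding statement tells the reader whether those who bring patients in could have been influenced by knowing the arm. Here allocation comes first, the practice learns of it, and only then are patients chosen. If practices in different strategies choose different kinds of patients, for example more or less motivated ones, the arms differ in case mix before any effect of support on patients is measured. Randomising practices does not protect against this, because the selection happens after randomisation.

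The first primary outcome is directly exposed because its denominator is the set of referred patients. A reader who takes the blinding statement at its word would credit the trial with a safeguard against this that it lacks.

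**Working it through.** The claim contains no figure to recompute, so the check is a comparison of the texts in the order of events.

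| Step | What the article says | Where | Does the practice know its own strategy? |
|---|---|---|---|
| 1. Allocation | "Prior to obtaining informed consent from GPs and patients, practices will be allocated to one of the strategies" | Study design | Not yet |
| 2. Invitation letter | "Practices will receive a letter containing information on the allocated implementation strategy" | Blinding and strategy allocation; also Table 1 | Yes, from here on |
| 3. Content of the letter (IS) | "General practices receive an invitation letter that includes all components of the Start-up Support Implementation strategy" | Start-up support package | Yes, with its components |
| 4. Practice consents | At least one GP must agree | Eligibility criteria general practices | Yes |
| 5. Patients chosen, invited, consented | "Patients will be enrolled by general practices" | Blinding and strategy allocation; Patients | Yes |
| 6. Strategy delivered | Start-up training in IS and ES; follow-up at one, three and five months in ES | Start-up support package; Practice coach package | Yes |

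From step 2 onward the statement "Both practices and patients will be blinded to group allocation" cannot be true of a practice's own allocation. The conflict lies within one section and again within one table. Each statement is a complete sentence made twice, so neither a slip in one place nor condensation for a journal explains it.

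**Patients.** The letter goes to practices. No section says that patients are told the strategy, and none says how they are kept from learning it. All are offered the same program and instruction visit. For patients the statement is therefore unsupported, not disproved.

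**Leverage on the first primary outcome.** Measurements and outcomes defines it as the proportion of referred patients who participate. With ten patients invited per practice, replacing one patient who would not participate by one who would moves that practice's proportion by 1/10 = 10 percentage points. Sample size calculation assumes 5% in the minimum strategy (MS) and an increase of 25%. Read as 25 points (5% against 30%), this reproduces the planned number:

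- 43 patients per arm before clustering (two-sided alpha 0.05, power 80%, continuity correction)
- design effect 1 + (10 − 1) × 0.25 = 3.25
- 43 × 3.25 = 139.75, so 140 per arm, or 14 practices of ten patients
- 140 × 3 = 420 in all

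No input to that calculation concerns blinding, so N and power do not change. The 10-point step shows only how sensitive the outcome is to who is referred. It does not estimate any bias that will occur.

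**The case against.** The strongest reply is that disclosure to practices is deliberate. The article randomises before consent so that practice uptake can be compared by strategy, and a practice must know its own offer to accept or decline it. In such a design, blinded may simply mean unaware that other strategies exist. This stands as a plausible account of what was meant, and no blinding that the design could have had has been lost. But the article never says it, and a reader would not take that meaning from the words used.

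Three stronger readings are tempting and are not supported:

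- *Patients are unblinded, so the self-reported AQLQ outcome suffers reporting bias.* Nothing shows that patients learn their strategy. The different questionnaire schedules by arm do not in themselves disclose it.
- *ACQ monitoring is biased because professionals encourage it.* Training, selection support and coaching are the components under test. Their effect on monitoring belongs to the strategy effect.
- *The study team helps choose patients only in IS and ES.* Start-up support package and Extended strategy (ES) read that way, but Table 2 marks on-site help with selection and invitation for all three strategies. A difference between arms in this help is therefore uncertain.

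It is also fair to say that rewording does not remove post-allocation selection, which comes from pre-randomisation combined with enrolment by practices. Rewording only stops the article from hiding it.

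**Conclusion.** The point holds for practices. They know their own strategy when they decide to join and when they select, invite and enrol patients, so the blinding statements in Blinding and strategy allocation and in Table 1 are wrong as written. For patients, blinding is asserted without support and remains open.

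The consequence is that patient selection may differ by strategy, bearing most directly on the first primary outcome through its denominator. All participating practices are exposed: 42 by Sample size calculation, or 3 × 12 = 36 by the count in Table 1. This describes exposure, not demonstrated bias. The article gives nothing from which to estimate a size, and the sample size stands.

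The conclusion assumes only that the letter says what the article says it does. It would not change if practices proved to be unaware of the other strategies, since they would still recruit knowing their own.

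**What to change.** 1. Replace the blinding statement in both places with wording such as: *Practices know their own allocated strategy from the invitation letter onward, including when they select, invite and enrol patients. Researchers are not blinded.* Add what practices know of the other strategies, and what patients know, only as the investigators confirm. The article supports no statement on either.
2. State that recruitment by practices aware of their own strategy is a source of selection bias.
3. Compare the characteristics of referred patients by strategy on data available in all arms. Study design and Endpoint evaluation assess MS patients only at six months, whereas Table 4 marks several baseline items for all strategies. Where MS baseline questionnaires are not collected, use practice registry data. Age and inhaled-corticosteroid or montelukast prescription must be known in every arm because they are eligibility criteria.
4. Optionally, run the primary analysis on coded strategy labels. This may not fully mask MS, because an arm with only six-month data would be recognisable.

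The cost is new wording in two places, one sentence on the limitation and one descriptive comparison, with some registry extraction if MS baseline data are absent. Design and sample size do not change.
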